### 12 months follow-up

Questionnaire and 7 day monitoring data will be collected at 12 months follow-up via post, 6 months after the intervention has ended.

### Sample size determination and power calculation

The sample size calculation was based on the primary outcome of feasibility of recruitment (assessed by recruitment rate). We aim to recruit 122 participants in total. This equates to 54 participants from the active surveillance group, 40 from the surgical group and 28 from the external beam radiotherapy/brachytherapy group. This allows for an anticipated 20% recruitment rate to be estimated with 95% confidence intervals from 15 to 25%, 14 to 26%, and 14 to 28%, respectively. This trial is not powered to assess any clinical effects, pharmacological effects, identify, verify or compare adverse reactions or study, verify or compare the interventions absorption, distribution, metabolism or excretion. It is not powered to ascertain, verify, or compare the efficacy of the intervention or safety of the intervention.

### Participant timeline

The participant pathway and data collection through the trial is presented in Fig. 1 and Table 1, respectively.

**Fig. 1 Fig1:**
[figure not shown]
Pre-EMpT participant flow diagram

### Plans for assessment and collection of outcomes

Data will be collected directly from participants with the except of data obtained from medical records (i.e. PSA level) or measured (i.e. height, weight) by the research nurse and reported on case report forms. Data quality will not be performed on the case report form data as the study is designed to assess the feasibility of collecting these data.

### Patient reported outcome measures (PROMs)

All participants will be asked to complete PROMs at baseline, 3, 6, and 12 months follow-up. These PROMs will be used to assess the feasibility of collecting these data from the study sample and will not be used to assess between-group differences. Table 2 provides a description of each of the PROMs.

**Table 2 Tab2:** Patient reported outcome measures

Questionnaire	Description of measurement	Measurement outcome
Godin Exercise Leisure-time Questionnaire	Number of times of mild, moderate, and strenuous physical activity for more than 15 min per week	Total leisure-time physical activity Categories: Active Moderately active Insufficiently active
International Continence Society male-Short Form (ICSmale-SF)	Urinary symptoms and impact on daily life in the last month	Voiding Incontinence
Profile of Mood States (POMS)	Frequency of 6 mood states over the past week	Tension Depression Anger Fatigue Confusion Vigour
Benefit Finding Scale	Personal growth and acceptance from a diagnosis of prostate cancer	Personal growth Acceptance
The Expanded Prostate Cancer Index Composite (EPIC-26)	Patient function and bother after prostate cancer treatment	Urinary incontinence Urinary obstructive/irritative Bowel Sexual Hormonal
Stages of change questionnaire	Five motivational stages of the transtheoretical model of behaviour change	Precontemplation Contemplators Preparation Action Maintenance
Theory of Planned Behaviour (TPB) questionnaire	Five constructs relating to the TPB	Attitude Perceived norm Perceived behavioural control Intention Past behaviour
Functional Assessment of Cancer Therapy-Prostate (FACT-P)	General health-related and prostate cancer-specific quality of life over the past week	Physical Social/family Emotional Functional Prostate cancer-specific scale
Functional Assessment of Chronic Illness Therapy-Fatigue (FACIT-Fatigue)	Impact of fatigue on daily activities and function over the past week	Overall fatigue score
EQ-5D-5L	Current health status	Mobility Self-care Usual activities Pain/discomfort Anxiety/depression Overall health status

### Tissue and blood sample collection

All human tissue samples are collected, used, and stored in accordance with the Human Tissue Act 2004.

Tumour tissue is extracted as per standard NHS protocols during the prostate biopsy taken at radical prostatectomy (surgical participants). Prostate tissue sections are formalin-fixed and prostate tissue that is surplus to diagnostic requirements will be stored for later research analysis. A small sample of prostate tissue is taken during the radical prostatectomy and transported directly to the study laboratory to be stored in a manner that preserves the genetic material.

Tissue, in the form of plasma, serum and whole blood, will be used to explore the feasibility of assessing the effects of physical activity and metformin interventions on biomarkers of prostate cancer (e.g. expression levels of IGF-I, metabolomic, and epigenetic profiles) using extracted genetic material (DNA/RNA) and the assessment of metabolites and proteins. Blood samples are collected for metabolomics, genetic and epigenetic (DNA, RNA) analysis, and other related research which may be conducted to investigate the feasibility of assessing biological mechanisms linking physical activity, metformin and other factors with prostate cancer risk and progression. Serum blood samples will be processed within 1.5 h from collection to freeze at − 80° centigrade for glycolysis assessment.

### Withdrawal and discontinuation of participants

Withdrawal of participants will be kept to a minimum through regular contact with the participants and ongoing motivational communication. However, participants may be withdrawn from the study by a member of their usual care team or a member of the research team if it is considered detrimental to the participants to continue. Additionally, a participant may withdraw from the study at any time without prejudice to his subsequent treatment. Participants who fail to attend appointments are contacted to encourage them to re-engage with the trial, and, where necessary, to determine reasons for withdrawal. Reasons for withdrawal (if provided) is fully documented, and any adverse events recorded if applicable. If participants switch to a different intervention, post-randomisation, primary outcome data will be analysed as per intention to treat.

### Data management

Personal identifiable data (e.g. names, mailing addresses) collected from the participants will be entered into an electronic database, which will be held securely and separately from other trial data. The database will be hosted by the university for the duration of the research. Access to the database will only be permitted to authorised staff. Anonymous data collected on the case report forms for the research clinic visits, questionnaires, and 7 day monitoring forms will be entered onto REDCap where data will be matched only to participants’ unique identifier. Data entry will be performed by authorised members of staff. Range checks will be performed on numerical values on data collected from the case report forms. Double data entry will be performed on a proportion of the data (e.g. 10%) collected from the questionnaire and 7 day monitoring form. The trial co-ordinator will be responsible for transferring and storing all paper records securely in the Trial office All paper records will be stored in a secure locked cabinet in a locked room and retained for 15 years following completion of the study.

### Confidentiality

Participants will be assigned a unique identifier on enrolled into the trial, which will be used on case report forms and self-report outcome measures to maintain participant anonymity. Personal identifiable data will be entered into an electronic database, which will be held securely and separately from other trial data. Anonymised data will not be shared with other researchers external to the study team.

### Analysis plan

The primary comparative analyses are by intention-to-treat for randomisation rates and adherence to treatment. Baseline characteristics for each group are tabulated using means and standard deviations for normally distributed data, medians and interquartile ranges for non-normally distributed data, and percentages and counts for categorical data. Outcome measures at baseline and follow-up are tabulated to assess the range of values to inform sample size calculations for a definitive trial. Secondary outcomes are tabulated as described above.

The measures made on the tissue and blood samples are research measures and do not have any direct clinical relevance for the participant or their routine clinic treatment. Analysis includes mean serum, plasma, and tissue levels of components of the IGF axis, including IGF-I as a biomarker of prostate cancer progression, and PSA level. Concentrations of IGF-I will be measured using gold standard ‘in-house’ radioimmunoassays. PSA levels will be measured using standard methods employed by the study’s NHS Pathology laboratory. Bloods and tissue may also be analysed for genetic, epigenetic, and metabolomic biomarkers.

Semi-structured face-to-face or telephone interviews will be conducted with participants to explore their experiences of their allocated intervention and the trial generally. Purposive sampling will be used to recruit up to 5 participants from each of the interventions, who underwent different treatment types and who wore the wearable activity tracker. The interviews will be audio-recorded, transcribed, anonymised, and analysed thematically using a qualitative method. A qualitative analysis computer program, such as NVivo [39], will be used to assist with the analysis.

### Composition of the coordinating centre

The day-to-day running of the trial will be supported by the Trial Management Group (TMG), which will be comprised of the Chief Investigators and the trial co-ordinator. The TMG will meet approximately once a month to monitor recruitment and data collection of the trial. We do not have a Trial Steering Committee. However, the Bristol Biomedical Research Centre management group, which includes workstream leads and management of the theme, will provide semi-independent oversight by reviewing recruitment and progress with the trial.

A prostate cancer Public and Patient Involvement group (PPI) has been involved in the development and delivery of Pre-EMpT. The group consists of participants who have or have previously had prostate cancer. They have been trained in different types of research methods and participant facing documents and they meet on a regular basis to discuss different aspects of the trial. This includes reviewing details of the interventions, testing data collection methods, and providing feedback on participant literature. If the trial experiences issues, for example, with recruitment, the group will explore possible barriers and solutions.

### Safety reporting

The Summary of Product Characteristics for Metformin (500 mg) is used as the Reference Safety Information for this trial. Adverse events (AEs) resulting from the intervention are recorded by the nurse or member of the research team; if an event is classified as serious (SAE), an assessment is made by the chief investigator as to whether the event is related to the study intervention and an 'unexpected' event. If an event is both related and unexpected it becomes a Suspected Unexpected Serious Adverse Reaction (SUSAR). These events are reported to the Sponsor immediately, and subsequent protocols followed.

The trial will be monitored in accordance with University Hospitals Bristol and Weston NHS Foundation Trust Monitoring and Oversight of Research Activity Standard Operating Procedure. The monitoring plan will be developed and agreed by the sponsor.

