### Trial design

Pre-EMpT has a multi-level 2 × 2 factorial design. Participants are randomised to both a physical activity level and a metformin level for 6 months. This results in four intervention groups, receipt of (i) both physical activity and metformin; (ii) physical activity only; (iii) metformin only; and (iv) neither intervention, used as the control (reference) group.

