### Randomisation and blinding

Randomisation will be stratified by treatment group (i.e. external beam radiotherapy/brachytherapy, radical prostatectomy and active surveillance). The research nurse will randomise participants after initial consent, but before main consent, using Research Electronic Data Capture (REDCap, [25, 26]) (a secure web-based system). The research nurse enters the new sequential participant ID and REDCap generates an intervention group for the new participant. This ensures allocation concealment from the nurses who assign participants to the intervention groups.

Participants, and the research team, are not blinded to the intervention allocation. Only those carrying out the analysis are blind to the intervention allocation.

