#### Control group

Participants randomised to the control group are asked to carry on with normal levels of physical activity. If participants ask for physical activity advice, standard, publicly available, information would be provided as per usual care.

These participants are not prescribed a placebo for metformin. This study is not designed to test the efficacy of the interventions compared to the control group.

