### Harms and provisions for post-trial care

Participants will be informed of the potential risks associated with the interventions before consenting to the trial. These risks include trips or falls and light muscle strain from brisk walking and nausea, diarrhoea, abdominal pain, appetite loss, and taste disturbance from taking metformin. There is no compensation for trial participation.

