#### Secondary outcomes

 Feasibility of assessing physical activity levels (self-reported at baseline, 3, 6, and 12 months follow-up and based on the Godin Exercise Leisure-time Questionnaire [28]);Intervention tolerability (qualitatively collected data, reporting of adverse events);Trial retention (number of participants successfully followed-up at the end of the 6 months active intervention element of the trial, as a proportion of those who we recruited to the trial and randomised into a study group at the start of the trial);Feasibility of measuring prostate specific antigen (PSA) level (measured at baseline and 6-months follow-up, collected via blood sample);Feasibility of measuring insulin-like growth factor I (IGF-I) (measured at baseline and 6-months follow-up, collected via blood sample);Feasibility of demonstrating methylation and gene expression profiles in blood (measured via blood and tissue (prostate tissue removed during surgery) as part of standard care) samples at baseline and 6 months follow-up);Urinary symptoms (collected at baseline, 3, 6, and 12 months follow-up and based on the International Continence Society male–Short Form, (ICSmale-SF) [29], and additionally collected at 7 weeks following main consent for participants undergoing surgery);Psychological factors (collected at baseline, 3, 6, and 12 months follow-up and based on the Profile of Mood States (POMS) [30] and Benefit Finding Scale [31]);Patient function and bother after prostate cancer treatment (collected at baseline, 3, 6, and 12 months follow-up and based on the Expanded Prostate Cancer Index Composite (EPIC-26) [32]);Health beliefs (collected at baseline, 3, 6, and 12 months follow-up and based on questionnaires measuring constructs of the transtheoretical model of health behaviour change (i.e. stages of change) [33] and the Theory of Planned Behaviour [34]);Quality of life measures (collected at baseline, 3, 6, and 12 months follow-up and based on the Functional Assessment of Cancer Therapy–Prostate (FACT-P) [35]);Cancer-related fatigue (collected at baseline, 3, 6, and 12 months follow-up and based on the Functional Assessment of Chronic Illness Therapy-Fatigue (FACIT-Fatigue) [36] and the EuroQol 5 dimensions questionnaire (EQ-5D-5L) [37], additionally collected at 4.5 months after main consent for participants undergoing external bean radiotherapy or brachytherapy);General lifestyle factors (self-reported levels of smoking and drinking); Feasibility of participants with localised prostate cancer wearing wrist worn activity trackers (assessed by qualitative interview and the 7 day monitoring form); Impact of wrist worn activity trackers on adherence to the physical activity intervention (assessed by step count on the 7 day monitoring form and data recorded by wrist worn activity trackers);Weight and body mass index (measured by a nurse);Attitudes and views of participants about the physical activity and metformin interventions and participation within the trial (based on qualitative interviews conducted once participants complete 6-months follow-up).

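### Adverse events are recorded on condition that unblinded staff attribute them to the intervention, so the adverse-event part of tolerability has no background rate

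*Protocol article*

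**What the plan says.** The Safety reporting section gives the general rule: "Adverse events (AEs) resulting from the intervention are recorded by the nurse or member of the research team". For an event classed as serious, the same sentence continues that "an assessment is made by the chief investigator as to whether the event is related to the study intervention and an 'unexpected' event". No causality step is described for non-serious events.

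Adverse events feed a named secondary outcome: "Intervention tolerability (qualitatively collected data, reporting of adverse events". The Analysis plan says secondary outcomes are tabulated.

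Three design features bear on this:

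- Trial design: one of the four factorial groups receives "neither intervention, used as the control (reference) group".
- Control group: "These participants are not prescribed a placebo for metformin".
- Randomisation and blinding: "Participants, and the research team, are not blinded to the intervention allocation".

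The Harms section lists the anticipated risks, beginning "These risks include trips or falls and light muscle strain from brisk walking and nausea, diarrhoea" and going on to other gastrointestinal and taste symptoms. The only other wording on recording events is in the section on withdrawal and discontinuation. It has any adverse events recorded when a participant withdraws and attaches no relatedness condition.

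**The concern.** A record of harms is normally built in two steps: capture what happened, then judge cause. Here the two are merged. An event is described as recordable because it resulted from the intervention, so someone has already judged cause, and that person knows the allocation.

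Two things are at stake:

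- **Tolerability.** Its adverse-event component becomes a count of events that staff attributed, with nothing from untreated men to set beside it. Several of the listed symptoms are non-specific, and 68 of the planned 122 men (40 surgery, 28 radiotherapy or brachytherapy) start radical treatment about a week after the baseline visit. Attributing a single event is therefore weak evidence.
- **Serious events.** If the condition is applied literally, an event that staff first judge unrelated might not reach the chief investigator, whose assessment is what identifies a related and unexpected serious event.

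**Working it through.** The point rests on wording, and the plan gives no figure to reproduce. The check sets the sections side by side and counts who can contribute events under the rule.

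**Step 1: order of judgement.**

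- Recording (Safety reporting): "Adverse events (AEs) resulting from the intervention are recorded by the nurse or member of the research team". The judgement of cause is made by the nurse or research team, who are unblinded.
- Review (Safety reporting): "an assessment is made by the chief investigator as to whether the event is related to the study intervention". The judgement is made by the chief investigator, for serious events only.

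The same question is the condition for entry and then the question asked. For non-serious events the first judgement is the only one described.

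**Step 2: who can contribute.** Inputs: planned total 54 + 40 + 28 = 122 (Sample size section) and four groups (Trial design). Equal allocation is my assumption, as the article gives no ratio.

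| Group | Metformin-attributed events | Walking-attributed events |
|---|---|---|
| Both | possible | possible |
| Walking only | none, by the rule | possible |
| Metformin only | possible | none, by the rule |
| Neither | none, by the rule | none, by the rule |

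- Neither group: 122 / 4 = 30.5, so about 30 men cannot contribute any event.
- Per intervention: 122 / 2 = 61, so about 61 men have a zero that reflects the rule and not their experience.

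**Step 3: what complete capture would give.** If all events were recorded, the no-metformin half would supply a background rate. Exact (Clopper-Pearson) 95% intervals, for assumed rates near 10% and 20%:

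| Men without metformin | Events | 95% interval |
|---|---|---|
| 61 (half of 122) | 6 (9.8%) | 3.7% to 20.2% |
| 61 | 12 (19.7%) | 10.6% to 31.8% |
| 55 (half of the 110 recruited, Trial status) | 6 (10.9%) | 4.1% to 22.2% |
| 55 | 11 (20.0%) | 10.4% to 33.0% |

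These intervals are wide and descriptive, but they are usable for planning. The written rule gives no estimate at all.

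**Step 4: does other text supply the missing rate?** The withdrawal wording covers only men who withdraw. The EPIC-26 bowel domain and FACIT-Fatigue are collected in all groups, but the article does not make them part of tolerability, and the section on patient-reported measures says they will not be used for between-group differences.

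**The case against.** The strongest reply is that the article condenses a fuller protocol (V6), which may define capture more broadly, and that the Sample size section says the trial is not powered to identify or compare adverse reactions. Both limit the point. The first does not remove it, because the article states a rule here; it does not merely leave one out. The second rules out inference between groups, but complete capture and a descriptive table need no power, and the trial exists to inform a definitive one.

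Three stronger readings are not supported:

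- **A reader might infer that serious events judged unrelated are certainly lost.** The sentence does not say that only attributed events are recorded. Its second half refers simply to an event classed as serious, and asking the chief investigator about relatedness makes most sense if possibly unrelated events do arrive. The loss is one reading of ambiguous text.
- **A reader might try to size the spurious difference between groups by applying a bowel-symptom rate during pelvic treatment to whole arms.** The article gives neither such a rate nor the fraction staff would attribute. Moreover, 54/122 (44%) are on active surveillance and only 28/122 (23%) are due radiotherapy or brachytherapy.
- **A reader might infer a safety gap because the reference safety information covers metformin only.** A related serious walking event absent from that reference would count as unexpected and go to the sponsor immediately, which is the cautious direction. Treating the Harms list as an expectedness reference would remove serious falls from that route, so it should not be used that way.

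**Conclusion.** The concern holds in limited form. As written, recording depends on attribution by unblinded staff, non-serious events have no stated later review of cause, and the adverse-event part of tolerability has no background rate. The size that can be shown is structural: a zero for all events in about 30 of 122 men, and for each intervention's attributed events in about 61 of 122. This assumes equal allocation and that the rule was followed literally. The resulting bias cannot be quantified from the article. For serious events the finding is that the text is ambiguous, not that cases are missed. Because the trial disclaims any comparison of safety, this is a cheap improvement that does not threaten the primary feasibility outcomes.

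**What to change.** Reword the Safety reporting section so that all serious events, and non-serious events of the types listed in the Harms section, are recorded in all four groups regardless of suspected cause. Relatedness is then assessed as a separate, later step. Tabulate events descriptively by allocated group and treatment pathway, with no test. Reconcile the wording with the unconditional wording in the section on withdrawal.

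Recruitment ended in March 2020 and data collection was expected to finish in March 2021, so capture may already be complete. In that case, state which rule was actually used. If it was broader than the article says, correct the text. If it was the written rule, label the data as staff-attributed events, do not present the control group's zero as a rate, and carry the reworded rule into the definitive trial.

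The cost is modestly more event forms at the 3- and 6-month contacts that every participant already has; if capture is over, it is a change of wording and labelling only.
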